**Trial Registration:**

ClinicalTrials.gov, NCT03261713. Registered on 21 August 2017. Registration amended on 1 June 2018 to decrease enrollment from 40 to 20 due to a cut in study funding and difficulty recruiting participants.

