The secondary objective is to assess the feasibility of the outcome measures, using quantitative and qualitative methods. Specific objectives are:To assess the feasibility and acceptance of a battery of outcome measures, including physical assessments, questionnaires, an interview and a log book;To assess the potential that home-based VRT might maintain or improve physical outcomes of standing balance, gait and general function and community integration after discharge from hospital-based stroke rehabilitation, compared to those who perform a program of iPad apps designed for fine hand motor skills and cognitive training;To determine the sample size required for a future definitive RCT on in-home VRT.

This study is a prospective, single-site, single-blinded, parallel-group (1:1 ratio) randomized, superiority feasibility trial on the use of VRT for ongoing stroke rehabilitation after discharge from inpatient or outpatient stroke rehabilitation. A feasibility RCT was chosen in order to provide the most useful results to prepare for a future definitive RCT on the efficacy of home-based VRT. iPad apps were chosen as a comparator to VRT because they provide a control group that has equal contact with the researchers and equal time spent in an engaging activity. The use of an active control group (rather than providing control group participants with nothing) was also chosen to facilitate recruitment. The iPad apps chosen to work on hand fine motor control and cognition were not deemed to have any influence on the physical outcome measures of standing balance, gait and gross motor function. The Standard Protocol Items: Recommendation for Interventional Trials (SPIRIT) checklist is available as Additional file 1: Figure S1.

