### Sample size and recruitment

No sample size calculation was performed as this is a feasibility trial. The sample size of two groups of 20 is based on available time and recruitment expectations and funding level. It is expected that having 20 participants in the VRT arm of the study will be enough to discern the feasibility of home-based VRT. It is deemed reasonable that 40 out of the estimated 375 stroke rehabilitation inpatients and the 375–450 patients who attend outpatient stroke rehabilitation over 18 months will be eligible and interested in the study. Members of the clinical care team will be made aware of the study through their clinical manager and attendance at team meetings. The study will be stopped prematurely if serious adverse effects occur.

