### Outcome measures

To address each primary objective as numbered, the following outcome measures are used:The number of participants recruited over 18 months will be determined relative to the number who met the study participation criteria and the number who were approached by the clinical staff and the RA. The inability to recruit at least 30 participants will require the researchers to alter recruitment procedures for a definitive RCT.Ability to comply with the research protocol will be assessed through notes taken by the research PT and comments provided by the participant and study partner in the log book, on the phone and at the interview. If a majority of participants perform less than 450 min of VRT over the 6 weeks (900 min is the requirement of the protocol), the use of VRT as a motivation to encourage people to exercise post stroke will be reconsidered and reasons why will be discerned. Retention of participants will be measured and a loss of more than 25% will suggest that changes should be made to the protocol.The presence of adverse effects will be recorded from telephone conversations with the participant and through the log book. The occurrence of major adverse effects (e.g. falls with serious injuries) would suggest that home-based VRT, as used in this protocol, is too risky to continue.Ability to use VRT in the home will also be assessed through comments written in the log book or made by the participants during VRT installation and follow-up phone calls and in the interview. Use and progression of the VRT program will be monitored asynchronously by the research PT. Poor learning would be implicated if no progression is observed. Also, expressions of frustration or confusion with the games will indicate poor ability to do VRT.Acceptability of VRT will also be assessed using information gleaned from the log books and follow-up phone calls and from the Physical Activity Enjoyment Scale, which rates (from 1 to 7) 18 statements of one’s feelings about physical activity (PACES) [20], administered at the post hoc assessment only.Costs related to the VRT equipment/licences, travel and salaries will be calculated, in order to prepare a budget for a definitive RCT.

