The following outcomes will be used to address each secondary objective.The first secondary objective (feasibility and acceptance of a battery of outcome measures) will be assessed by recording the completion of 11 outcome measures, including physical outcomes (5 tests), questionnaires (4 in total), a log book and a semi-structured interview. The inability of all participants to complete the outcome measures, within a reasonable time frame (2 h) will result in re-thinking the use of each measure in a definitive RCT.The potential for VRT to maintain or improve standing balance, gait, general function and community integration post stroke will be assessed with the following tests:Berg Balance Scale (BBS) [21]. The BBS tests balance and mobility using 14 items scored from 0 to 4.Timed Up And Go (TUG) [22–24]. The TUG assesses the time required to stand up, walk 3 m, return and sit down. There are 3 versions, original, manual (performed while holding a cup of water) and cognitive (performed while also doing a cognitive task).Five Times Sit-To-Stand Test (FTSST) [25]. The FTSST tests the time it takes to stand up from a chair and sit down again five times.Community Balance and Mobility Scale (CB&M) [26]. The CB&M assesses more difficult balance tasks that are relevant to community ambulation.Quantitative analysis of quiet stance and limits of stability in standing [27]. These tests provide quantitative information about the neural mechanisms of postural control [1].Stroke Impact Scale (SIS) [28]. The SIS assesses health status after stroke.Reintegration to Normal Living Index (RNLI) [29]. The RNLI assesses the degree to which individuals have reintegrated back into normal social activities after illness. It has acceptable reliability and validity.

All of these scales have adequate to excellent reliability, validity and responsiveness to change (except responsiveness to change for the FTSST) [26, 28, 30–36].The Motivation for Physical Activity Questionnaire will be administered before the VRT protocol only, to better describe the participant sample [37].3.The results of the BBS will be assessed and used to calculate an effect size in order to estimate the sample size for a definitive RCT.

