The results of this study will be submitted as a manuscript to a relevant journal and presented at the 2019 Canadian Stroke Congress and also at smaller, local meetings and rounds. Wider dissemination of the research to the stroke research community, clinicians and the public will be provided by the Canadian Partnership for Stroke Recovery and also by Bruyère Continuing Care, along with its collaboration with local news organizations.

One limitation of this feasibility RCT is its small sample size. While it is appropriate to do a feasibility study before time and funds are committed for a definitive RCT, this will limit its ability to detect significant differences between groups.

Looking ahead from this feasibility study, we will plan a definitive study to test the efficacy of home-based VRT in improving physical outcomes (standing balance, gait and overall function). The preliminary results will inform the future RCT about such parameters as sample size, control intervention, primary and secondary outcome measures, number of weeks of VRT, length of VRT sessions and number per week. Practical information such as recruitment rate and costs will also be important to inform a future proposal. We are currently engaged in knowledge translation research teaching of occupational therapists, physiotherapists, rehabilitation assistants and recreation therapists to use VRT in the clinic and have plans to expand further into this area. In the future we hope to add the home-based component to the clinician training.

There is an escalating trend toward increasing the use of technology in the home. Home-based VRT is poised to follow this trend, with the expectation that it will increase rehabilitation intensity and lead to improved functional outcomes after stroke.

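### The definitive RCT is to be sized from the BBS effect size observed here, an estimate too imprecise for that use at 20 or about 10 per arm

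*Protocol article*

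**What the plan says.** All references are to the protocol article.

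- **Introduction and objectives.** The third secondary objective reads "To determine the sample size required for a future definitive RCT on in-home VRT". The design is a "parallel-group (1:1 ratio) randomized, superiority feasibility trial".
- **Outcome measures.** The method for that objective is fixed: the BBS results are "used to calculate an effect size in order to estimate the sample size for a definitive RCT".
- **Sample size and recruitment.** "No sample size calculation was performed as this is a feasibility trial", and "The sample size of two groups of 20 is based on available time and recruitment expectations and funding level".
- **Trial Registration.** "Registration amended on 1 June 2018 to decrease enrollment from 40 to 20", which is about 10 per arm at 1:1. The Abstract's Methods and the sample size section still give 40.
- **Outcome measures, on retention.** "a loss of more than 25% will suggest that changes should be made to the protocol", so a loss of up to a quarter is tolerated. Data management and analysis specifies complete cases, so each loss shrinks the sample behind the effect size.
- **Discussion.** The small sample is acknowledged: "this will limit its ability to detect significant differences between groups". The same section says the preliminary results will inform the future trial's sample size. It does not connect the two statements.

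The article nowhere gives a target BBS difference, a confidence limit or shrinkage to apply to the observed effect, or a rule for a null or negative estimate.

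**The concern.** The required sample size varies with the inverse square of the effect, so error in the effect is magnified in the sample size. An observed effect about 1.4 times the true one halves the planned trial. An observed effect at or below zero gives no sample size for a superiority trial at all. With 10 to 20 per arm, chance errors of that size are common.

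At stake is one of the main products of this feasibility trial. The stated method can hand the next team a sample size that looks evidence-based but does not deliver its nominal power. The problem lies in the use made of the estimate, not in the small size of a feasibility trial.

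**Working it through.** The article contains no power or effect-size calculation, so there is no figure of its own to reproduce.

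**Inputs from the article.** 20 per arm (Sample size and recruitment); about 10 per arm (Trial Registration, 20 in total at 1:1); up to 25% loss, giving 15 per arm or 7 to 8 per arm.

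**Assumptions, because the article gives none.** The effect size is a between-group standardized difference d; the definitive trial uses two-sided 5% and 80% power; the true d is 0.3, 0.5 or 0.8; outcomes are normal.

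**Step 1: interval around one estimate.** For an observed d of 0.5, the exact noncentral-t 95% CI is -0.13 to 1.13 at 20 per arm and -0.40 to 1.38 at 10 per arm. Planned n per arm = 2(1.96 + 0.8416)²/d² = 15.70/d².

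- Point estimate: 15.70/0.25 = 62.8, so 63 per arm.
- Upper limit: 15.70/1.13² = 12.3, so 13 per arm (20-per-arm pilot); 15.70/1.38² = 8.2, so 9 per arm (10-per-arm pilot).
- Lower limit: negative in both cases, so no finite n.

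**Step 2: when the rule fails.**

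- *No computable n.* P(observed d ≤ 0) = Φ(-d√(n/2)). For d = 0.5: Φ(-1.58) = 0.057 at 20 per arm and Φ(-1.12) = 0.13 at 10 per arm.
- *True power below 50%.* By the normal approximation this happens when d√(n/2) < 1.96, that is n < 7.68/d². Setting 15.70/d_obs² < 7.68/d² gives d_obs > 1.43 × d. For a true d of 0.5, any observed d above about 0.71 plans such a trial.

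**Step 3: how often.** 200,000 simulated pilots per scenario, with the Hedges-corrected observed d put into the formula of step 1 and the true power of the resulting n computed at the true d:

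| True d | Pilot n per arm | No computable n | True power below 50% | Either |
|---|---|---|---|---|
| 0.3 | 20 | 17.1% | 33.8% | 51% |
| 0.3 | 10 | 25.2% | 37.5% | 63% |
| 0.5 | 20 | 5.7% | 23.7% | 29% |
| 0.5 | 10 | 13.0% | 29.9% | 43% |
| 0.8 | 20 | 0.6% | 14.9% | 16% |
| 0.8 | 10 | 3.7% | 22.0% | 26% |

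At a true d of 0.5, where 63 per arm are needed, the middle half of the computed sample sizes runs from 30 to 153 per arm (20-per-arm pilots) or 23 to 156 (10-per-arm pilots).

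**Step 4: sensitivity at d = 0.5.** With a 25% loss the combined share rises to 8.5% + 26.6% = 35% (15 per arm) and 17.4% + 32.3% = 50% (7 per arm). With a 90% power target and no loss it falls to 20% (20 per arm) and 35% (10 per arm).

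**Step 5: the alternative.** Fix the target difference and take only the SD from this trial, at its one-sided 80% upper limit. The multiplier is √(df/χ²₀.₂₀,df): 1.12 for df = 38 (N = 40) and 1.18 for df = 18 (N = 20). Baseline adjustment costs one more df, which leaves 1.12 and gives 1.19. For an illustrative target of 0.5 SD, 62.8 × 1.1155² = 78.1, so 79 per arm, and 62.8 × 1.1832² = 87.9, so 88 per arm. A finite n always results.

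**The case against.** The strongest reply is that one clause in a condensed article is being read as a complete rule. It does not say that the raw point estimate will be used alone, or whether the effect is between groups or pre-post, and the Discussion says only that results will inform the sample size. Alpha, power and any margin belong to the future trial's own protocol. This has some force, and it is why the percentages are conditional on stated assumptions. But the article names the quantity to be used and its purpose, and nothing in it tempers that. A pre-post effect would not rescue the method, since it would include change unrelated to VRT.

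The size of the problem also depends on the unknown true effect. That stands: at d = 0.8 with 20 per arm the combined risk is about 16%, and a null or negative estimate alone is the rarer failure (6% to 13% at d = 0.5).

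Three stronger readings are tempting but not supported:

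- *The carried-forward effect is biased upward, because only a promising pilot leads to a definitive trial.* The decision thresholds under Outcome measures concern recruitment, minutes of VRT, retention, adverse events and completion of the measures. None uses an efficacy result, and the Discussion plans the definitive study without an efficacy condition.
- *The BBS has a ceiling that distorts the effect.* The scale is bounded (14 items scored 0 to 4, maximum 56), but the article gives no BBS distribution, and it describes the scale's responsiveness as adequate or better.
- *The authors concede that the trial cannot detect group differences.* They say only that its ability to do so is limited.

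**Conclusion.** The concern holds as a matter of precision. The article states a method for sizing the definitive RCT, and at 20 or about 10 per arm that method would often mislead. The share of pilots giving no sample size, or a trial with true power below 50%, is about 29% to 43% at a true d of 0.5, 51% to 63% at 0.3, and 16% to 26% at 0.8. The lower figure in each pair is for 20 per arm.

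These figures rest on an assumed between-group standardized effect, two-sided 5%, 80% power, normal outcomes and no loss; a 25% loss makes them worse. They do not show that the estimate is biased, only that it is very imprecise.

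The change should be made, but it is not critical. It touches the third secondary objective, and no participant, randomization step or primary feasibility outcome of this trial is affected. The harm would arise in the next trial.

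**What to change.** Reword the third secondary objective's method under Outcome measures along these lines:

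1. The definitive RCT will be sized on a target between-group BBS difference, fixed in advance as the smallest difference judged worthwhile.
2. This trial will supply only nuisance quantities: the BBS SD with an allowance for its imprecision (for example its one-sided 80% upper limit, about 1.12 times the observed SD at N = 40 and 1.18 to 1.19 times at N = 20), the pre-post correlation and the loss rate.
3. The observed BBS effect will be reported with its 95% CI, as descriptive only.

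The 80% limit is one convention among several; what matters is that some allowance is named beforehand.

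Cost: one paragraph of wording and no new data. The target difference must be justified from outside this trial, because the article gives none. The planned sample size will usually be larger: in the illustration above, 79 or 88 per arm instead of 63.

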### Procedures and participant timeline

Participants in both groups (and their study partners) attend a total of 4 sessions at Élisabeth Bruyère Hospital (see Fig. 2). The first 3 sessions occur a week or two before discharge from inpatient or outpatient rehabilitation. At sessions 1 and 2, each lasting 45–60 min, participants and their study partners are trained on how to use the VRT system or iPad and how to play the games. They are also instructed what to do if something goes wrong (for example, if the participant falls or the equipment did not work). Participants are given an instruction manual. Pre-outcome measures are performed by the RA at a third session, lasting approximately 1½ h.

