### Randomization, allocation and blinding

Participants are enrolled by the RA. A computer-based randomization system (Sealed Envelope, London, UK) is used to allocate participants in a 1:1 ratio to either experimental or control groups, using permuted blocks while maintaining concealment. The research physiotherapist (PT) accesses the system immediately after the participant is enrolled; the allocation is provided immediately. The only person blinded to treatment allocation is the RA, who performs the outcome measures. The research PT is blinded to the results of the outcome measures. If the participant is undergoing rehabilitation during the study period (for example, outpatient or community-based rehabilitation), the rehabilitation professional is informed of their patient’s participation in the study, to ensure that the home-based exercise is compatible with the participant’s therapy. The PT will reveal a participant’s allocation in the case of serious adverse effects.

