**Fig. 2 Fig2:**
[figure not shown]
Schedule of enrolment, interventions, and assessments

After assessment, the research PT visits the participant’s home to install the equipment and finish training. The games, safety considerations and follow-up procedures are reviewed with the participant and his or her study partner. Participants in both groups are instructed to perform their exercises five times a week for 6 weeks. VRT sessions are designed to run for approximately 30 min of activity time and participants in the iPad group are asked to use it for at least 30 min a day. This amount of additional training (15 h) has been shown to produce a significant improvement in activities of daily living post stroke [38]. The study partner must be in the home of the participant while he or she is doing VRT.

All participants are contacted by the research PT via telephone or email twice a week for the first week and at least once a week for the following 5 weeks to offer encouragement, suggest modifications to the games and identify any safety issues or technical problems. Participants are also invited to contact the research PT as needed. For those in the experimental group, the research PT monitors the compliance and success rate of VRT at least once a week using the remote access feature of the VRT system, and can modify the games if necessary.

Participants in both groups are provided with a logbook in which to record technical issues with the VR equipment, thoughts on how the games are going and if progression was required, safety concerns and adverse events and changes to the exercise environment. Those in the control group must also record the time spent on the iPad apps each day and which apps are used. Participants are encouraged to do as many activities of daily living (ADL) and instrumental ADLs as they wish, including walking, participation in exercise groups and therapy. Throughout training and during the intervention, every attempt is made to equalize contact time with the research personnel between the two groups.

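### The 'pre' outcome scores are taken after allocation is disclosed and after two arm-specific training sessions, so the pre-post contrast may miss early VRT gain

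*Protocol article*

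**What the plan says.** Under Randomization, allocation and blinding, the protocol article has the research associate (RA) enrol the participant, and then: "The research physiotherapist (PT) accesses the system immediately after the participant is enrolled; the allocation is provided immediately". The same section states: "The only person blinded to treatment allocation is the RA, who performs the outcome measures". Participants and their partners therefore know the arm from the outset.

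Under Procedures and participant timeline, three hospital sessions come before discharge. The first two, of 45 to 60 minutes each, are for training. Their content is described thus: "participants and their study partners are trained on how to use the VRT system or iPad and how to play the games". The baseline follows: "Pre-outcome measures are performed by the RA at a third session". The home phase starts later still: "After assessment, the research PT visits the participant’s home to install the equipment and finish training".

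Data management and analysis compares each scale by a mixed ANOVA with time, group and their interaction. Outcome measures uses the BBS result to derive an effect size, and from it the sample size of a definitive trial. No earlier baseline is described. Fig. 2 is not reproduced in the text at hand, but the prose leaves no doubt about the order.

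**The concern.** In a pre-post interaction the baseline score is subtracted. This recovers the full effect of allocation only if the baseline was measured before allocation could act on it. Here it could already have acted in two ways.

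- **Exposure.** One arm has had up to two sessions with games that train standing balance, stepping and reaching. The other has had iPad apps, which the Introduction regards as having no influence on the physical outcomes. Any early gain therefore falls on one side only.
- **Knowledge of the arm.** The Stroke Impact Scale and the Reintegration to Normal Living Index are answered by participants who know their allocation. The motivation questionnaire, later a regression predictor, is in the same position if it is given at session 3.

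At stake is the BBS effect size carried into the definitive trial. If that trial copied the schedule, it would inherit the same baseline. More participants do not remove a bias of this kind.

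**Working it through.** **Order of events.** Setting the two sections side by side gives: enrolment → allocation disclosed → training session 1 → training session 2 → 'pre' scores (session 3) → home installation and remaining training → six weeks at home → 'post' scores. Training differs by arm, so allocation must be known before session 1.

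**What the interaction estimates.** Let D be the full VRT effect since randomization and g the part already present at session 3, with no such part in the control arm.

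Interaction = (post − pre in VRT) − (post − pre in control) = D − g.

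**Inputs.**
- Training before baseline: 2 × 45 to 2 × 60 = 90–120 min (Procedures and participant timeline).
- Home dose: 6 weeks × 5 sessions × 30 min = 900 min. This reproduces the protocol's own figure: "900 min is the requirement of the protocol" (Outcome measures).
- The plan states no sample size calculation, alpha, power, effect size or SD. These are assumed below for illustration only.

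**Share of exposure before baseline.**
- Relative to the home dose: 90/900 = 10.0% to 120/900 = 13.3%.
- Relative to training plus home: f = 90/990 = 9.1% to 120/1020 = 11.8%.

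The training completed at home has no stated length and comes after baseline. Counting it would lower f slightly.

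**Consequence if gain is proportional to session time (assumption).**
- Effect retained: 1 − f = 900/990 = 0.909 to 900/1020 = 0.882.
- Inflation of the derived sample size: 1/(1 − f)² = (990/900)² = 1.21 to (1020/900)² = 1.28.
- Example with an assumed true standardized effect of 0.5, two-sided alpha 0.05, power 0.80 and SD 1: n per arm = 2(1.96 + 0.84)²/d², giving 63 undiluted and 76–81 after dilution.
- If instead g = 0, the retained effect is 100% and the inflation is 1.00.

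**Scale against random error.** At a true effect of 0.5 SD, the dilution is 0.5 × 0.091 = 0.05 SD to 0.5 × 0.118 = 0.06 SD. The 95% half-width of a standardized difference is about 1.96 × √(2/n). That is 0.62 SD at 20 per arm (40 planned) and 0.88 SD at 10 per arm (registration amended to 20 in total). Sampling error is about ten times the dilution or more.

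**The case against.** The order of events cannot be disputed, but much can be said about how far it matters.

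- **The exposure is a ceiling.** A reader might infer that the VRT arm has completed 1.5–2 h of active balance games. The article does not say so. The sessions also teach partners, cover what to do after a fall or equipment fault, and include handing over a manual. The 900 min, by contrast, is activity time. This objection stands, and the 9–12% compares session length with activity time.
- **Early gain may be nil.** The Discussion holds that some 15 h of additional exercise is needed to increase function. On that premise, under two hours of partly verbal instruction may add almost nothing. Front-loaded learning would push the other way. The documents settle neither, so it cannot be said outright that the estimate is biased.
- **Attenuation would be conservative.** It would lead to a larger next trial, not a false claim of efficacy. This stands for the BBS but not for self-reports, where the direction is open.
- **A later baseline sits nearer the home phase.** Assessing first puts slightly more hospital rehabilitation inside the pre-post change. That is true, but it falls on both arms alike.

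Three further inferences are tempting and are not supported. Assessor bias at baseline does not follow: the RA is stated to be blinded, and also meets participants after six weeks of training, so this order adds little risk. Early leavers are not lost because of the order: they lack a post score whichever way the visits run, so complete-case analysis drops them regardless. An invalid baseline covariate is not at issue, because the plan adjusts for none.

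**Conclusion.** The point holds as a possible bias of unknown size. The baseline is post-randomization, follows VRT exposure in one arm only, and is taken with participants aware of their arm. For the BBS and other physical measures, attenuation is the plausible direction; for self-reports it could go either way.

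The range for the BBS runs from about none to an effect about 9–12% too small and a derived sample size 1.21–1.28 times too large. The upper end rests on two assumptions: gain proportional to session time, and the whole of both sessions counted as exposure.

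A reader might infer that this undermines the trial. It does not. The six primary objectives (recruitment, compliance, safety, usability, acceptability and cost) are unaffected, and the article already concedes limited ability to detect group differences. What it does not acknowledge is this source of systematic error in the figure meant to size the next trial. It should be fixed, but the trial does not fail without the change.

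**What to change.** Keep the same visits and staff but change the order: consent and the RA's baseline assessment first; then randomization by the research physiotherapist; then the two arm-specific training sessions. The eligibility criteria already require two assessment and two training appointments, so no visit is added. The cost is some rescheduling and a slightly earlier baseline relative to discharge.

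For participants already enrolled under the present order:
- flag them in the data and the report;
- state that the contrast covers only change after training;
- add, as a sensitivity analysis, a between-arm comparison of post scores that leaves out the 'pre' score. This targets the full effect since randomization, at a price in precision. With equal variances and pre-post correlation ρ, a change score has variance 2σ²(1 − ρ) against σ² for the post score, so the post-only comparison is the less precise when ρ exceeds 0.5;
- report by arm how many were lost between randomization and session 3. This is for transparency, since reordering would not restore their post scores.

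Recruitment began in May 2017 with an 18-month window, so the reordering may reach few participants in this trial. The corrected order should in any case be written into the definitive trial, and the BBS effect size should be passed on with this limitation attached.
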